#### Pre-session voice recording and stabilization before each session

Participants receive brief study explanations before donning Head-Mounted Displays (HMD) and physiological monitoring equipment (Shimmer3 GSR + unit; Shimmer Sensing, Dublin, Ireland). Following equipment setup, participants produce 1) a 5-s sustained vowel/a/(“ah ~ ”; the central 3 s analyzed) and 2) a continuous reading passage from the standardized Korean paragraph “Fall” (Kim, 1996; see Appendix A for full text, IPA transcription, and English translation), which provides balanced phonemic coverage and is widely used for voice and speech assessments [36]. These recordings will be analyzed for fundamental frequency (F0), intensity, pause duration, and speech rate as baseline prosodic indicators. The sustained vowel duration aligns with CAPE-V recommendations for stable phonation [37]. The passage length was selected to ensure sufficient voiced material for reliable acoustic and temporal analyses, as long-term speaking-rate measures typically stabilize within ~8–16 s [38].

After the voice recording, participants undergo a 3-min stabilization period during which they fixate on a small black dot displayed at the center of a blank VR screen. This stabilization phase allows physiological indicators to reach baseline levels and facilitates adaptation to the VR environment. The interview simulation then proceeds automatically. At Session 1, these measures form part of the study baseline assessment (T0); analogous pre-session recordings in Sessions 2 and 3 are used only for within-session standardization and are not additional baseline assessments.

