#### First session

When the VR content begins, participants first wait in a virtual waiting area where they receive entry guidance through on-screen and audio instructions. After this brief orientation, the interviewer requests a brief self-introduction. Upon receiving the question, participants are given a 20-s preparation period (indicated by an on-screen countdown timer) to organize their thoughts before beginning their response. Participants then present for 1 min while monitoring a timer interface. In the experimental group (EG) intervention, the interviewer demonstrates positive reactions such as nodding while listening to participants’ self-introductions and responds with “Yes, I heard you well.”, “Please relax and feel free to speak comfortably.” upon presentation completion. In the control group (CG), interview questions are provided through automated voice prompts, with no visual or auditory interviewer reactions provided. Both groups participate in a 2-min “positive self-talk session” immediately following presentation simulation, after which equipment is removed and questionnaire surveys are completed. Participants are scheduled to revisit the laboratory for the second session after 48 h (± 2 h). Figure 2 shows screen captures of what participants observe through VR.

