#### Second session

Participants undergo the same stabilization session as the first session before proceeding with the interview. In the experimental group, the interviewer requests an explanation of strengths and weaknesses with a neutral expression. Participants receive a 20-s preparation period followed by 1 min for their presentation. The interviewer maintains neutral observation of the participant before examining application materials and responding “Hmm… I see” upon presentation completion. In the control group, interview questions are provided through automated voice prompts with no visual or auditory interviewer reactions. Both groups participate in a 2-min “worry reflection and acceptance practice” immediately following presentation simulation.

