#### Exploratory variables

Behavioral indicators: Intervention effects on behaviors such as movement and vocal changes are examined in exploratory analyses. Movement is collected through fixed cameras filming participants’ upper body frontal views, with Motion Energy Analysis (MEA) used to analyze synchronization patterns with VR interviewer movements [49]. Synchronization patterns are modeled as sine wave dynamics, with amplitude and vertical offset parameters extracted as indicators of interpersonal coordination quality [49]. These synchrony metrics are correlated with session-specific anxiety levels (derived from concurrent physiological and self-report measures) and compared across sessions and participants to examine relationships between social synchrony and anxiety reduction.

Voice data from presentation speech are collected through VR microphones during sessions. Prosodic voice features such as fundamental frequency (f0), intensity contours, pause time, and speech rate will be extracted from recordings during pre-session stabilization. Speech samples will be preprocessed with noise filtering but not segmented into fine-grained phonetic units. Recordings are captured using the Meta Quest 3 headset’s built-in microphone (mono, 48 kHz). Acoustic analyses will be conducted in Praat (v6.3 or later), and all acoustic features will be standardized within participants relative to the pre-session baseline to control for inter-individual variability.

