Motion Energy Analysis (MEA) quantifies movement patterns using 10 frames per second video conversion and gray-scale pixel differencing methodology [49]. Motion energy vectors undergo standard smoothing and z-transformation procedures. Given that control group interviewers remain static, synchronization analysis focuses on within-experimental group patterns. Following established MEA protocols, 4-min interaction segments (question → presentation → interviewer reaction) are analyzed using 30-s sliding windows with cross-correlations computed for time-lags up to ±5 s in 0.1-s steps [49].

Voice analysis examines 1-min presentation recordings using automated prosodic feature extraction. Speech samples will be preprocessed with noise filtering but not segmented into fine-grained phonetic units, as analyses focus on suprasegmental prosodic patterns. Primary measures include fundamental frequency (F0) mean, speech rate, and pause ratio, which together reflect expressive and arousal-related vocal behavior. All features will be within-subject standardized relative to baseline readings to control for inter-individual variability. Voice features will be compared between groups and across sessions, with correlation analyses examining relationships between prosodic stress indicators (e.g., elevated F0, reduced speech rate, increased pause ratio) and concurrent anxiety measures. Expected patterns include higher F0 and slower, less fluent prosodic dynamics in early sessions, followed by progressive normalization indicating reduced performance anxiety [53].

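### Two exploratory analyses do not match the session described: the 4-min motion-energy segment is about twice as long as the interaction, and one section takes voice features from a phase with no speech task

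*Protocol article*

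**What the plan says.** **Movement.** Under *Data preparation and planned analyses*, "4-min interaction segments (question → presentation → interviewer reaction) are analyzed using 30-s sliding windows". The same paragraph sets the video at 10 frames per second and, because the control interviewer does not move, limits the analysis to one arm: "Given that control group interviewers remain static, synchronization analysis focuses on within-experimental group patterns".

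The session descriptions give the timings. In *First session*, "participants are given a 20-s preparation period", and then "Participants then present for 1 min while monitoring a timer interface". In *Second session*, "Participants receive a 20-s preparation period followed by 1 min for their presentation". *Third session* has the same 20 s and 1 min. Each session has one question and a short scripted reaction, and a 2-min coping exercise follows once the simulation has ended. That exercise is self-talk in session 1, worry reflection in session 2, and breathing and muscle relaxation in session 3.

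**Voice.** *Exploratory variables* first says that voice data come from the presentation. It then says that the prosodic features "will be extracted from recordings during pre-session stabilization", and that all features are standardized to the pre-session baseline. *Pre-session voice recording and stabilization before each session* places a sustained vowel and a reading passage first; after these, "participants undergo a 3-min stabilization period during which they fixate on a small black dot". *Data preparation and planned analyses* says: "Voice analysis examines 1-min presentation recordings using automated prosodic feature extraction".

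**The concern.** Both points concern parameters that the article itself fixes, so they are not details left to a fuller plan.

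For movement, a segment defined by its content (question, answer, reaction) is given a length that this content cannot fill. An analyst who takes the length literally would clip 240 s and so include the coping exercise, during which there is no interview to synchronize with. Because the exercise changes from session to session, and *Exploratory variables* compares synchrony across sessions, part of any session difference could come from the exercise.

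For voice, two sections name different source recordings for the same features. If the outcome came from the pre-session block, it would come from the block that also supplies the reference, and it would carry no information about speech under exposure.

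**Working it through.** **1. Length of the MEA segment**

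Stated figure: 4 min × 60 = 240 s.

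Inputs from the session descriptions (the same in all three sessions):
- preparation 20 s
- presentation 60 s
- question and reaction: no duration given
- coping exercise 2 min = 120 s, after the simulation and outside the stated segment

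Timed content: 20 + 60 = 80 s. If preparation is not counted, it is 60 s and the gap is larger.

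Question and reaction time needed to reach 240 s: 240 − 80 = 160 s.

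To judge whether 160 s is plausible, count the words of the scripted lines in the article's English and assume 100 to 150 words per minute:
- session 1 reaction: 13 words, 5.2 to 7.8 s
- session 2 reaction: 3 words, 1.2 to 1.8 s
- session 3 question: 18 words, 7.2 to 10.8 s
- session 3 reaction: 25 words, 10.0 to 15.0 s

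The longest scripted pair, in session 3, takes at most 10.8 + 15.0 = 25.8 s. Allowing for non-verbal behaviour, I assume 10 to 40 s for question and reaction together:
- lower end: 80 + 10 = 90 s (1.5 min)
- upper end: 80 + 40 = 120 s (2.0 min)

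The 4-min figure is therefore not reproduced. It is 240/120 = 2.0 to 240/90 = 2.7 times the described interaction.

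Share of a literal 240-s clip outside the interaction:
- (240 − 120)/240 = 50%
- (240 − 90)/240 = 62.5%

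Adding the coping exercise gives 80 + 120 = 200 s, and a further 40 s of question and reaction gives exactly 240 s. So a 4-min clip starting at question onset would take in the whole exercise under these assumptions.

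Number of 30-s windows, sliding one frame at a time at 10 frames per second (the step is my assumption; lag margins ignored), is 10T − 300 + 1 for a segment of T seconds:
- T = 240: 2400 − 300 + 1 = 2101
- T = 120: 1200 − 300 + 1 = 901
- T = 90: 900 − 300 + 1 = 601

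**2. Source of the voice features**

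No arithmetic applies. Set side by side:
- *Pre-session voice recording and stabilization*: vowel and reading are recorded first; 3 min of dot fixation follow, with no speech task described.
- *Exploratory variables*: speech is collected during the presentation, but features are extracted from stabilization.
- *Data preparation and planned analyses*: features come from the 1-min presentation and are standardized to the baseline readings.

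The first and third agree with each other. The extraction sentence in *Exploratory variables* conflicts with both, and with the sentence that opens its own paragraph.

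**The case against.** **The segment is defined by content, so the coping exercise is already excluded.** This stands in part. A reader might infer that MEA scores, computed as the article describes, must include minutes with no partner. That does not follow, because the stated parts end with the interviewer's reaction. The harm arises only if the length is followed rather than the content. But the article states both, and they cannot both hold.

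**Question and reaction times are assumed.** This is correct. In addition, session 3 ends with a request for more detail, and an untimed second answer could lengthen that session. Nothing similar is described for sessions 1 and 2, and the shortfall there is still 160 s before question and reaction are counted.

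**The voice phrase is loose wording for the pre-session block.** This is plausible, since the feature list nearly matches the one given for the pre-session recordings. A reader might infer that the voice analysis rests on recordings that the session never produces. The documents do not support that: the sessions yield both the 1-min presentation and the baseline reading, and the analysis section uses them. Silence during fixation is implied, not stated. What remains is one sentence naming the wrong source, and on the loose reading it would still be wrong for an outcome.

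**Synchrony has no chance reference.** A reader might count this as a further error, since synchrony is analysed in one arm on a shared script. The documents do not establish one. The article follows a cited MEA procedure, and a condensed article may leave surrogate handling to the full plan. It does not say whether signed, absolute or peak correlations are used. Absolute and peak values exceed zero by chance, whereas signed means of unrelated series do not carry that upward bias. A script common to all experimental participants also does not by itself create a correlation between synchrony and anxiety across participants.

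**Conclusion.** The concern holds as two contradictions within the article. First, the 4-min MEA segment does not fit the session: 80 s are timed, and the whole interaction lasts about 90 to 120 s if question and reaction together take 10 to 40 s. The conclusion is not sensitive to that range, since 240 s would need 160 s of question and reaction against scripted lines of at most about 26 s. Second, one sentence takes the prosodic features from a phase with no speech task, while the analysis section takes them from the presentation.

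Both should be corrected before recordings are processed. The consequence is limited to exploratory movement and voice results; the primary PSAS analysis and the sample size do not depend on them.

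**What to change.** 1. In *Data preparation and planned analyses*, replace the 4-min figure with a segment bounded by events: from question onset to the end of the interviewer's reaction, excluding the coping exercise. Use only 30-s sliding windows that lie wholly inside it, and report the achieved segment length by session. State whether any further answer in session 3 is included. If the interaction is in fact longer than the session descriptions imply, those descriptions need to be reconciled with this section.

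2. In *Exploratory variables*, correct the extraction sentence: outcome features come from the 1-min presentation, and the standardization reference is the reading recorded before stabilization.

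3. Optional, not an error to correct: add a chance-level reference for synchrony, for example by pairing control participants' movement with the experimental interviewer's animation. Limit this to phases with shared timing, because the arms diverge once the interviewer reacts.

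Items 1 and 2 cost a few sentences and a rule for cutting existing recordings. Item 3 adds some computation on existing video. None needs new data.

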#### Third session

Participants proceed with interviews following the stabilization session. In the experimental group, the interviewer displays a tired expression, sighs, makes notes on paper, and asks “Next, please tell me about the two most memorable news items you’ve seen recently and explain your reasons.” After a 20-s preparation period, participants present for 1 min. During the participant’s response, the interviewer begins whispering to another interviewer, then responds with negative expression and voice tone upon response completion: “I can’t hear your voice well, so please speak a little louder and more clearly. Also, could you explain what you mentioned in more detail?” In the control group, interview questions are provided through automated voice prompts with no visual or auditory interviewer reactions. Both groups participate in a 2-min “breathing and muscle relaxation training” immediately following presentation simulation. Across groups, the interview topics, preparation time, speaking duration, and session sequence are identical; only the interviewer reaction format differs between conditions. The positive, neutral, and negative interviewer reactions were designed as sequential components of a single graded exposure intervention rather than as separate intervention arms. Figure 3 shows the intervention process and questionnaire administration timepoints.

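### In the exploratory voice analysis, a session-to-session trend within an arm is read as falling anxiety, although the speaking topic changes with every session

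*Protocol article*

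**What the plan says.** All references are to the protocol article.

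- **Material and comparisons.** Data preparation and planned analyses states: "Voice analysis examines 1-min presentation recordings using automated prosodic feature extraction". The main measures are mean F0, speech rate and pause ratio. It continues: "Voice features will be compared between groups and across sessions".
- **Interpretation.** The same paragraph says how the course over sessions is expected to look and what it would mean: "Expected patterns include higher F0 and slower, less fluent prosodic dynamics in early sessions, followed by progressive normalization indicating reduced performance anxiety".
- **Topics.** In First session, "the interviewer requests a brief self-introduction". In Second session, "the interviewer requests an explanation of strengths and weaknesses with a neutral expression". In Third session the prompt is "please tell me about the two most memorable news items", with reasons. Third session also says that topics, preparation time, speaking time and session order are the same in both arms.
- **Constant-text recording.** Before every session participants read the same standard Korean paragraph, and voice features are standardized to the baseline reading. Under Pre-session voice recording and stabilization before each session, the "analogous pre-session recordings in Sessions 2 and 3 are used only for within-session standardization and are not additional baseline assessments".
- **Status and limitations.** Exploratory variables classes vocal measures as exploratory. The limitations in the Discussion acknowledge the fixed order of interviewer reactions. They do not mention that the topic changes too.

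**The concern.** Introducing oneself, describing strengths and weaknesses, and recalling and justifying two news items after 20 seconds of preparation are different speaking tasks. Speech rate and pausing can depend on what is being said. If they do, a within-arm change from Session 1 to Session 3 mixes a topic effect with any change in anxiety. This holds in the control arm as well, where there are no interviewer reactions.

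The plan nevertheless settles in advance that movement towards fluent speech means less performance anxiety. A harder third topic could hide real improvement, and an easier one could produce apparent improvement. The Discussion presents the physiological and behavioural indicators as a way of tracking anxiety objectively, so a topic artefact could end up reported as objective support for desensitization.

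**Working it through.** **1. Is topic separable from session?** The design has one topic per session, in the same order for everyone. Take a model with an intercept, group (1 column), session (2), topic (2) and group-by-session (2):

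- columns: 1 + 1 + 2 + 2 + 2 = 8; rank: 6;
- without the two topic columns: 6 columns, rank 6.

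Topic is fully aliased with session. Group and group-by-session remain estimable.

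**2. What each contrast contains.** Let a(s) be the anxiety-related level at session s and t(s) the topic effect, with t(s) common to both arms.

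- Within an arm, Session 3 minus Session 1: [a(3) − a(1)] + [t(3) − t(1)]. Only the sum can be estimated.
- Experimental change minus control change: the term t(3) − t(1) appears in both arms and cancels.

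**3. Does standardization help?** Let r(s) be the pre-session reading. Its text is constant, so it carries no topic effect. The standardized change is [a(3) − r(3)] − [a(1) − r(1)] + [t(3) − t(1)]. The last term is untouched. The subtraction may also remove any session-to-session fall in arousal already present in the reading.

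**4. How large could this be?** The protocol gives no topic effect and no figure for the voice analysis, so the following is an illustration on assumed values.

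- *Sample size.* The Sample size section gives 78 analysed and 92 recruited. These reproduce: repeated-measures interaction with f = 0.15, six measurements, correlation 0.50 and ε = 0.50 gives power 0.801 at N = 78 (0.790 at 76), and 78/0.85 = 91.8, rounded up to 92. Per arm that is 39 completers or 46 recruited.
- *Assumed.* Within-person correlation 0.5. The protocol uses this value for the PSAS sample size, not for voice. Topic shift d = 0.2, 0.3 or 0.5 SD from Session 1 to Session 3, with no change in anxiety.
- *Formula.* SE = √(2(1 − 0.5)/n) = √(1/n). At correlation 0.5 the SD of the paired difference equals the SD of one measurement, so d is the same on either scale. The probability of a two-sided p < 0.05 is Φ(d/SE − 1.96) + Φ(−d/SE − 1.96).

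| n | SE | d = 0.2 | d = 0.3 | d = 0.5 |
|---|---|---|---|---|
| 39 (one arm, completers) | 0.160 | 24% | 47% | 88% |
| 46 (one arm, recruited) | 0.147 | 27% | 53% | 92% |
| 78 (both arms, completers) | 0.113 | 42% | 76% | 99% |
| 92 (both arms, recruited) | 0.104 | 48% | 82% | about 100% |

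Example for n = 46, d = 0.3: 0.3/0.147 = 2.03, and Φ(2.03 − 1.96) ≈ 0.53; the second term is negligible.

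**The case against.** **The randomized comparison is sound.** Topics and their order are the same in both arms, and a between-group voice comparison is already planned. This stands. A reader might infer that the voice analysis as a whole, or the trial's main conclusion, is confounded by topic. The protocol does not support that: topic cancels between arms, voice is exploratory, and the primary PSAS analysis does not use it.

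**The sentence is an expectation, not a test.** This is also true, and it keeps the point small. But the sentence says what the pattern would indicate, and the design cannot support that meaning. Exploratory status does not repair an interpretation fixed in advance.

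**The constant-text readings are used.** A reader might infer that the only comparable voice data are discarded. They are not: the readings serve as the standardizer, and the restricting sentence can be read as protecting T0 as the single study baseline. Nor would they be a clean substitute for the presentations. The reading comes before the interview, with no question and no listener, so it reflects an anticipatory or resting state. It is also the same paragraph read three times within about a week, so familiarity is tied to session just as topic is.

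**The percentages prove nothing about topic.** This is correct. They show what an assumed shift would do, not that one exists or in which direction it runs. The argument is also stronger for speech rate and pausing than for mean F0.

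**Conclusion.** The point holds, and its severity is minor. Within an arm, the session trend in presentation speech is completely aliased with topic, so it cannot be taken as evidence of reduced performance anxiety. Standardization does not change this, and the stated limitation covers only the order of reactions. The aliasing follows from the design and needs no assumption. Its practical size is unknown: the 24% to 92% single-arm range in the table rests on assumed shifts of 0.2 to 0.5 SD and an assumed correlation of 0.5. That the between-arm contrasts are clean rests on the topic effect being the same in both arms. Any modification of it by the interviewer's reactions would form part of the package effect being estimated.

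**What to change.** 1. In Data preparation and planned analyses, delete the statement that normalization across sessions indicates reduced performance anxiety. Report within-arm session trends as descriptive, and state that topic changes with session.
2. Base voice inference on between-arm contrasts (group at the same session, and group-by-session), read as the effect of the overall graded package, in line with the limitation already stated in the Discussion.
3. Optional: relax the restriction on the Session 2 and 3 readings so that they can be reported as a supplementary across-session series compared between arms. State that they reflect anticipatory or resting state and may show repetition effects, and that they do not replace the presentation speech.
4. Reconcile Exploratory variables, which has the prosodic features extracted from pre-session recordings, with Data preparation and planned analyses, which takes them from the 1-minute presentations.

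The cost is wording only, since the recordings are already planned in both arms. What is given up is the within-arm claim of normalization in presentation speech.
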